# Follow-up study of infants recruited to the randomised, placebo-controlled trial of azithromycin for the prevention of chronic lung disease of prematurity in preterm infants—study protocol for the AZTEC-FU study

**DOI:** 10.1186/s13063-022-06730-x

**Published:** 2022-09-21

**Keywords:** Neonates, Preterm, Azithromycin, Neurodevelopment, Chronic lung disease, Bronchopulmonary dysplasia, Respiratory

## Abstract

**Background:**

Preterm birth, especially at less than 30 weeks’ gestation, is significantly associated with respiratory, neurodevelopmental and growth abnormalities. The AZTEC study has recruited 799 infants born at < 30 weeks’ gestation to determine if a ten-day intravenous treatment with azithromycin improves survival without development of chronic lung disease of prematurity (CLD) at 36 weeks’ post menstrual age (PMA) when compared to placebo. The follow-up studies will compare respiratory, neurodevelopmental and growth outcomes up to 2 years of corrected age between infants who received azithromycin and those who received placebo in the early neonatal period.

**Methods:**

Survivors at 36 weeks’ PMA from the main Azithromycin Therapy for Chronic Lung Disease of Prematurity (AZTEC) study with parental consent will continue to be followed up to discharge from the neonatal unit and to 2 years of corrected age. Length of stay, rates of home oxygen, length of supplemental oxygen requirement, hospital admissions, drug usage, respiratory illness, neurodevelopmental disability and death rates will be reported. Data is being collected via parentally completed respiratory and neurodevelopmental questionnaires at 1 and 2 years of corrected age respectively. Additional information is being obtained from various sources including hospital discharge and clinical letters from general practitioners and hospitals as well as from national databases including the National Neonatal Research Database and NHS Digital.

**Discussion:**

The AZTEC-FU study will assess mortality and important neonatal morbidities including respiratory, neurodevelopmental and growth outcomes. Important safety data will also be collected, including the incidence of potential consequences of early macrolide use, primarily pyloric stenosis. This study may have implications on future neonatal care.

**Trial registration:**

The study was retrospectively registered on ISRCTN (ISRCTN47442783).

## Background

Survival from preterm birth, especially at extremes of gestation, has improved significantly over the last 20 years [1]. However, survivors of preterm birth remain at risk of significant longer-term morbidity including for neurodevelopmental, respiratory and growth outcomes. Chronic lung disease of prematurity (CLD), also known as bronchopulmonary dysplasia, results from multiple exposures resulting in pulmonary inflammatory injury to the structurally immature lungs with subsequent altered lung growth which can adversely affect longer term lung function [2]. Despite advances in neonatal intensive care, CLD remains a significant medical concern, and rates have not improved significantly, possibly due to improved survival of more extremely immature infants (< 26 weeks’ gestation) [3]. Despite CLD being a diagnosis of the neonatal period, it is associated with longer term morbidity including increased hospitalisation in infancy [4, 5], increased wheezing and other respiratory symptoms [6] and decreased lung function [6–9]. The reduction in lung function is increasingly thought to have significant health implications for the individual’s lifespan, with premature development of chronic obstructive pulmonary disease (COPD) now considered a potential outcome of developing CLD in infancy [10].

Neurodevelopmental delay is another significant adverse outcome in survivors of preterm birth, with increased rates of cerebral palsy and moderate to severe developmental disability frequently noted at 2-year corrected gestational age [11, 12]. Risk factors for the development of CLD, such as low gestation, prolonged duration of respiratory support following birth, are also associated with poorer neurodevelopmental outcomes [13], and there is a strong association between CLD and longer-term adverse motor and cognitive function [14] and reduced IQ [15].

An additional adverse outcome after preterm birth is poor somatic growth. Postnatal growth is often compromised for preterm born infants, due to an immature gastrointestinal system, prolonged periods of parenteral nutrition, increased energy requirements especially during periods of illness, periods of fluid restriction and feed intolerance or due to gastrointestinal disorders such as necrotising enterocolitis. Preterm-born infants often continue to have reduced growth velocities leading up to discharge. Following discharge, infants, especially those who had CLD, are at high risk of poorer growth attainment [16]. Reduced head growth has been shown to have a link with later neurodevelopmental conditions such as cerebral palsy [17].

There have been many attempts to improve these outcomes. Azithromycin is a commonly prescribed antibiotic in the paediatric and adult populations for respiratory conditions associated with infection and inflammation such as cystic fibrosis [18] and COPD [19] and has been shown to improve the long-term outcome for these patients. In the paediatric population, use of macrolides such as erythromycin and azithromycin, may be associated with a small risk of complications such as cardiac rhythm abnormalities and pyloric stenosis [20], but it is unclear if these risks extend to the preterm neonatal population, and a recent systematic review did not find any such evidence [21]. The main azithromycin therapy for chronic lung disease of prematurity (AZTEC) trial has monitored these potential complications.

Azithromycin is attractive as it is active against *Ureaplasma* spp. which has been implicated in the development of CLD [22] and has potent anti-inflammatory effects which may target the pulmonary inflammation that is often observed at 7–10 days of age in preterm-born infants who develop CLD [23, 24]. Interestingly, azithromycin use has also shown improved neurodevelopmental outcomes in animal models of neuro-injury. In one study, 30 mg/kg azithromycin administered to neonatal rat model with right carotid ligation and 8% oxygen hypoxic exposure resulted in less functional defects, less weakness in left paw grip and less right hemisphere damage, in the treated group when compared to the placebo group [25]. In another study, azithromycin (20 mg/kg for 2 days) resulted in physiological (decreased paresis and co-ordination deficits) and histological (decreased ventriculomegaly and neuronal necrosis/apoptosis) improvements in a neonatal mouse model of periventricular leukomalacia [26].

The AZTEC study is an adequately powered phase III randomised, placebo-controlled trial examining whether a 10-day course of early azithromycin improves rates of survival without CLD in infants born at < 30 weeks’ gestation [27]. The primary outcome is survival without development of CLD when the active and placebo arms are compared. Secondary outcomes include rates of CLD and severity at 36 weeks’ PMA, mortality by 36 weeks’ PMA, number of days of respiratory support/oxygen-dependency, development of complications of prematurity, serious adverse events/reactions and resistance to macrolides in lung and stool samples [27]. It will also investigate the extent to which the outcomes differ dependent on whether the participants’ lungs were or were not colonised with baseline *Ureaplasma* spp.

It will be important to follow these infants beyond 36 weeks’ PMA to monitor any longer-term effects from the early use of azithromycin and ensure longer term safety. The AZTEC follow-up studies (AZTEC-FU) are assessing death rates, respiratory, neurodevelopmental and growth outcomes for AZTEC study participants from 36 weeks PMA up to 2 years of corrected age. Additional mechanistic elements are investigating underlying mechanisms of azithromycin action by studying the effects of azithromycin on the lung and stool microbiome, tracheal aspirate cytokines and proteome, and on antibiotic resistance against azithromycin in lung and stool samples obtained in the first 3 weeks of life.

## Methods/design

### Main objectives

The main objectives of the AZTEC-FU study are to compare respiratory, neurodevelopmental, growth and mortality outcomes at 1 and 2 years of corrected age in infants who received azithromycin or placebo in the early neonatal period.

The specific aims are to compare between the treated and placebo groups (Fig. 1):

**Fig. 1 Fig1:**
[figure not shown]
SPIRIT figure

Mortality:Total number of deaths occurring from birth to 1- and 2-years of corrected age will be reported as will those occurring (a) from birth to 36 weeks’ PMA (which will have been reported in the AZTEC trial), (b) 36 weeks to never discharged and (c) after discharge.

Respiratory:

The main outcome will be parent reported wheezing at 1 year of corrected age. The following outcomes will also be reported:Length of the initial neonatal stay in hospitalNumber of infants discharged home on domiciliary ambulatory oxygenLength of oxygen supplementation (including at home)Parent reported wheeze from discharge to 2 years of corrected ageNumber of respiratory hospital admissions up to 1 year and 2 years of corrected ageNumber of prescribed respiratory drugsSurvival (from birth) without parent reported wheeze at 1 year of and 2 years of corrected age

Neurodevelopmental:

The main outcome will be survival (from birth) without combined moderate/severe neurodevelopmental disability at 2 years of corrected age. The following outcomes will also be reported at 2 years of corrected age:Moderate/severe neurodevelopmental disabilityThe proportion of infants who develop moderate-severe neurodevelopmental impairment, defined as Parent Report of Children’s Abilities–Revised (PARCA-R) questionnaire score of < 44Overall motor score as well as fine and gross motors scoresOverall language scores as well as expressive and receptive language scoresOverall cognition score

Combined moderate/severe neurodevelopmental will be defined, as previously [28, 29] as any of the following:Moderate or severe visual impairment (reduced vision uncorrected with aids, blindness in one eye with good vision in the contralateral eye or blindness or light perception only)Moderate or severe hearing impairment (hearing loss corrected with aids, some hearing loss uncorrected by aids, or deafness)Moderate or severe gross motor impairment (inability to walk or sit independently)Moderate or severe cognitive impairment will be defined using PARCA-R or by using clinical data if PARCA-R scores are missing. Total PARCA-R scores of less than 44 (range, 0 to 158, with lower scores indicating greater impairment) will be used to identify children with moderate or severe developmental impairment

Growth:Weight, height and head circumference will be reported at 1 and 2 years of corrected age after adjusting for sex and gestation

Adverse eventsWe shall also report the rates of reported pyloric stenosis in the active treatment and placebo groups at 1 year of corrected age

Biological sample analysis:The respiratory and stool samples collected during the AZTEC trial [27] will additionally be analysed to investigate whether, when compared to the placebo group, azithromycin alters the cytokine, proteomic and microbiome profiles in lung or stool samples as well as any modification that occurs in those colonised by *Ureaplasma* spp

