### Design

AZTEC is a double-blind, randomised, placebo-controlled trial using azithromycin or placebo as previously described [27]. The AZTEC-FU study will continue to follow-up the infants recruited to AZTEC up to 2 years of corrected age. The participants and researchers will continue to remain blinded for the AZTEC-FU study.

Data between 36 weeks’ PMA and discharge from the neonatal unit are collected from a dedicated discharge clinical record form (CRF), neonatal discharge summaries and clinic letters, data held in the National Neonatal Research Database (NNRD) and from the parents. When the infants enrolled in the AZTEC trial reach 1-year and 2-years of corrected age, we are contacting the parents/guardians by mailing them validated (a) respiratory and (b) neurodevelopmental questionnaires. In addition, we are asking the parents/guardians for (c) information on any hospital admissions and (d) growth data of their babies from the Red Book system in the UK, which records growth data by Health Visitors, and at local hospital follow-up clinics. An option is available to complete the questionnaire on a secure online site. In parallel, we are contacting local hospitals for clinic letters from which relevant data are extracted: including (a) respiratory symptoms, (b) developmental progress, (c) growth, (d) hospital admissions, and (e) any medication especially respiratory and antibiotic usage. In addition, we are also contacting the General Practitioners for clinic letters, discharge summaries and a copy of the GP record for the children to provide an additional route to collect the above information. Data will also be obtained from NHS Digital for information on hospital admissions and outpatients’ attendances and from the data held in the National Neonatal Research Database (NNRD) at Imperial College, a central repository where most of the UK neonatal units send their clinical data [30] (Fig. 2).

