#### Questionnaires at 1- and 2-year’s corrected age

For those who consented to follow-up, a questionnaire including a covering letter explaining the study, an information sheet explaining the questionnaire, a stamped questionnaire return envelope and a voucher to thank the parents for their baby’s participation in the study are mailed. The letter also contains a personalised quick response (QR) code and website URL link which they can use if they wish to complete the questionnaire via a secure online website (Online Surveys, Jisc, Bristol, UK).

The questionnaire at 1-year corrected age captures respiratory symptoms, the infant’s and family history of atopy, number of course of antibiotics, number of hospital admissions, maternal smoking during pregnancy and current smoking in the family who share the house with the infant, information on siblings, as well as general developmental questions and entries for the infant’s weight, length/height and head circumference. The questionnaire also specifically asks if the infant has had pyloric stenosis [21].

At 2 years of corrected age, the questionnaire captures the same information as year one, but with greater detailed neurodevelopment data captured via using the PARCA-R questionnaire which has been validated against Bayley’s Scales of Infant Development Version III assessments [31].

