#### Data from general practitioners

At 1 and 2 years of corrected age for the infants whose parents/guardians have consented to the AZTEC-FU study, the GPs are contacted for copies of the infant’s notes including medical or surgical consultations, hospital discharge summaries and outpatient clinic or in-patient letters. Data is being extracted from these records by the AZTEC-FU study team including information on number of hospital admissions, diagnoses, duration of home oxygen therapy (if applicable) and drug history.

Data held in the NNRD which collates neonatal data provided for each neonatal admission by almost all neonatal units in the UK. Data collected includes information on initial neonatal admission as well as neurodevelopmental data at 2 years of corrected age, most commonly assessed by using Bayley’s Scales of Infant Development Version III, but during and after the COVID-19 pandemic many units are increasingly using PARCA-R as a screening tool. Data held in the NNRD is being provided annually for each infant recruited to the AZTEC trial for infant’s whose parents/guardians have provided appropriate consent.

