#### Statistical analysis

A statistical analysis plan will be developed prior to the end of the study. Baseline descriptors will be given. Data analyses will be conducted to identify any differences in the respiratory, neurodevelopmental, and growth outcomes, as well as hospital admissions between the placebo and the treatment group using two-by-two tables and chi-square testing. We shall consider *p* < 0.05 as statistically significant and report 95% confidence intervals. We shall also model the data, as in our previous publications [6], to identify early life factors that may result in long-term respiratory/neurodevelopmental abnormalities including presence/absence of *Ureaplasma* spp. at baseline before intervention commenced in the neonatal period; and if the treatment effect is influenced by early life factors, e.g. gestation, sex, and use of mechanical ventilation. Initially, we shall report the univariable data with a view to including any relevant factors into a model (using linear or logistic regression as appropriate). Missing data will be included in the analysis as missing data.

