
Neurodevelopmental outcome following preterm birth is a key metric for parents and the neonatal community [39]. Preterm birth is inherently associated with increased risk of poorer neurodevelopment [11, 12], with a strong association, and shared risk factors, between CLD and functional and cognitive outcomes [15]. Human studies have shown that azithromycin is widely distributed in the brain tissue [40], with animal models suggesting that azithromycin may also confer neuroprotective benefits. However, human data for the neuroprotective efficacy of azithromycin is currently lacking. Whilst we postulate improved neurodevelopmental outcomes at 2-year corrected age for those infants treated with azithromycin, we shall also investigate if there are detrimental neurodevelopmental effects from the early use of early azithromycin by using two-tailed comparisons. With our anticipated 500 responses, we have estimated that we should be able to detect 12.7% differences for the main respiratory and neurodevelopmental outcomes at 1 and 2 years of corrected age respectively.

The AZTEC-FU studies are also monitoring survival up to 2 years of age, separately reporting deaths at important timepoints up to 2 years of corrected age. Growth is another important postnatal factor, with preterm infants having poorer inpatient growth velocities [41], and those with CLD were noted to have poorer growth once discharged home [16]. We are collecting anthropometric measurements, including weight, length and head circumference at discharge, and over the first 2 years of life from routine clinic appointments and health visitor assessments. If azithromycin proves effective at reducing rates of CLD, it will be important to assess whether that confers growth benefits following discharge home.

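### Growth at 1 and 2 years is adjusted for sex and gestation, but the values come from routine records made at varying ages, and age at measurement is not in the named adjustment

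*Protocol article*

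**What the plan says.** The Growth item under Main objectives in the Protocol article fixes both the nominal ages and the adjusters: "Weight, height and head circumference will be reported at 1 and 2 years of corrected age after adjusting for sex and gestation".

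The sources of the values are given elsewhere in the article:

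- **Design:** parents are asked for "growth data of their babies from the Red Book system in the UK, which records growth data by Health Visitors", and for measurements from local hospital follow-up clinics. Hospital and GP letters are further sources.
- **Questionnaires at 1- and 2-year's corrected age:** the form has "entries for the infant’s weight, length/height and head circumference".
- **Discussion:** anthropometry is collected at discharge and "over the first 2 years of life from routine clinic appointments and health visitor assessments".

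The request is tied to age: "When the infants enrolled in the AZTEC trial reach 1-year and 2-years of corrected age, we are contacting the parents/guardians by mailing them" the questionnaires. That dates the request, not the measurement that is then copied from a record.

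The Statistical analysis section compares outcomes, growth among them, "using two-by-two tables and chi-square testing", mentions linear or logistic regression for modelling, and says that a SAP will follow. It does not mention age at measurement.

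**The concern.** Infants between discharge and 2 years are growing quickly, so a child measured a month or two later is longer and heavier for that reason alone. If values labelled as 1-year or 2-year were taken at different ages, part of the spread between children is spread in age. Gestation at birth does not measure this: two infants of the same sex and gestation can be weighed at different corrected ages.

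Growth is one of the stated main objectives, and the Discussion wants to know whether less chronic lung disease (CLD) brings better growth after discharge. Leaving age spread in the residual widens the confidence interval for that comparison, and the loss can be avoided with information that routine records normally carry beside the value.

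**Working it through.** **The plan's own figures.** The article states no SD, effect size or power for growth, so there is no growth figure to reproduce. The nearest is the detectable difference of 12.7 percentage points with 250 per group at power 0.80 and alpha 0.05 (Sample size; Tables 1 and 2). With the continuity-corrected two-proportion formula, 65% against 52.3% needs 251 per arm and 50% against 62.7% needs 254. The figure reproduces and is not disputed. It is used here only for the 250 per arm, and assumes that growth data are available for about as many children.

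**Inputs that are assumptions (near 12 months).**

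| Measure | Gain per month | SD between infants at a fixed age |
|---|---|---|
| Length | 1.2 cm | 2.7 cm |
| Head circumference | 0.45 cm | 1.4 cm |
| Weight | 0.25 kg | 1.1 kg |

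The SD of age at measurement is also unknown; 1, 2 and 3 months are shown.

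**Formula.** Let r = (gain per month × SD of age) / SD at a fixed age. If age is left out of the model, the variance is multiplied by 1 + r², so the usable information is 1 / (1 + r²).

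Length:
- Age SD 1: r = 1.2/2.7 = 0.44, r² = 0.20, information 1/1.20 = 84%.
- Age SD 2: r = 2.4/2.7 = 0.89, r² = 0.79, information 1/1.79 = 56%.
- Age SD 3: r = 3.6/2.7 = 1.33, r² = 1.78, information 1/2.78 = 36%.

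All three measures:

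| SD of age | Length | Head | Weight |
|---|---|---|---|
| 1 month | 84% | 91% | 95% |
| 2 months | 56% | 71% | 83% |
| 3 months | 36% | 52% | 68% |

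**In terms of power.** With age accounted for, 250 per arm detects (1.960 + 0.842) × √(2/250) = 0.251 SD at 80% power. If age is ignored, power for that same difference is Φ(2.802/√(1 + r²) − 1.960):

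| r | Effective n per arm | Power |
|---|---|---|
| 0.1 | 247.5 | 79.6% |
| 0.2 | 240 | 78.4% |
| 0.3 | 229 | 76.5% |
| 0.5 | 200 | 70.7% |

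For length on the assumed values, r = 0.44 gives about 73% and r = 0.89 about 55%.

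**Could age differ by arm?** The conceivable route runs from azithromycin to CLD to the timing of visits. The main trial was sized for a 12-point effect on survival without CLD; take that as a rough CLD difference. A gap of 0.5 month in mean age between the arms would then need infants with CLD to be measured 0.5/0.12 = 4.2 months earlier or later than the others, on average. A 1-month gap between infants with and without CLD gives 0.12 month between arms, that is 0.12 × 1.2 = 0.14 cm of length, or 0.14/2.7 = 0.05 SD. A systematic shift of 0.05 SD would raise a 5% rejection rate to 8.7%. This shows what would be needed; it is not evidence that it happens.

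**What a hard window would cost.** If measurement ages are normal around the target, a window of ±3 months excludes about 13% of values at an age SD of 2 months (beyond ±1.5 SD) and about 32% at 3 months (beyond ±1 SD).

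**The case against.** The strongest reply is that measurement windows, date matching and z-scores are usual SAP content, that the article condenses a fuller protocol, and that a one-line outcome description is not a model specification. The phrase about sex and gestation could even be shorthand for sex-specific scores at corrected age. Part of this stands: the article does not say that age will be ignored, and the Discussion's remark about measurements across two years does not say that any of them may serve as the 1- or 2-year value. But the article does not merely stay silent. It names an adjustment set, and an analyst who followed it would leave age out. A SAP can mend this later only if measurement dates have been captured.

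The second reply is that the sizes rest wholly on assumed growth rates, SDs and age spreads, and cover 12 months only. That stands. If growth has slowed by 24 months, the loss there for a given age spread is smaller. The 56% and 36% for length need an age SD of 2 and 3 months.

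Two stronger readings are tempting, and the documents support neither:

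- **Bias between arms.** A reader might infer that the growth comparison is biased because infants with CLD are seen on a different schedule. Randomisation and double blinding continue in follow-up, nothing in the article shows different measurement ages, and an important shift would need a large timing gap between infants with and without CLD.
- **The same fault in PARCA-R.** A reader might extend the point to the raw cut-off: "Total PARCA-R scores of less than 44 (range, 0 to 158, with lower scores indicating greater impairment". Parental completion is tied to a mailing at 2 years corrected age, the cut-off belongs to a definition used before, and cognition is one of four components of an outcome that also counts deaths. Some units also supply data ("many units are increasingly using PARCA-R as a screening tool"), but no effect of age at completion can be sized from the article.

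**Conclusion.** The point holds for growth, as a matter of precision. The named adjustment omits age at measurement although the values come from routine records, and gestation cannot replace it. On assumed 12-month values, the usable information for length falls to about 84% at an age SD of 1 month and 56% at 2 months; for head circumference to 91% and 71%; for weight to 95% and 83%. If the true spread is small (r of 0.1 to 0.2), the loss is slight, with power of 79.6% to 78.4% instead of 80%. The actual spread is not known from the article. A difference in age between arms remains possible but not shown, and no change is claimed for PARCA-R. Growth has no power statement and is not one of the two outcomes used for sizing, so this is a worthwhile, inexpensive improvement and does not threaten the study's main conclusions.

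**What to change.** Under Main objectives, Growth, replace the present adjustment with wording to this effect: the date of each measurement is extracted with its value; each value is converted to a sex-specific z-score for exact corrected age on that date; for each child the value nearest 12 or 24 months corrected age is used; and z-scores are compared between the arms. An acceptable alternative is to keep the sex and gestation adjustment and add corrected age at measurement to the model.

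Use a restricted window, such as ±3 months, only as a sensitivity analysis. As a main rule it could discard 13% to 32% of values if the age SD is 2 to 3 months, and the age-specific scores already deal with the spread.

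The cost is recording a date alongside each value and a routine conversion. Values without a date are lost. The change should be settled while the study team is still blinded.

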### Trial intervention

As previously described [27], infants born at < 30 weeks’ gestation, within 72 h of birth, were treated intravenously for ten days with 20 mg/kg azithromycin for 3 days, followed by a further 7 days of 10 mg/kg or with similarly constituted and administered placebo.

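### The stated covariate set for growth is sex and gestation; naming birth weight as well, in a prespecified linear model, would recover a modest amount of precision

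*Protocol article*

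**What the plan says.** All references are to the protocol article.

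- **Main objectives, Growth:** "Weight, height and head circumference will be reported at 1 and 2 years of corrected age after adjusting for sex and gestation". No other covariate is listed for growth.
- **Statistical analysis:** differences in outcomes, growth among them, are to be identified "between the placebo and the treatment group using two-by-two tables and chi-square testing". A modelling step follows: "Initially, we shall report the univariable data with a view to including any relevant factors into a model (using linear or logistic regression as appropriate"). The factors named as possible modifiers of the treatment effect are "early life factors, e.g. gestation, sex, and use of mechanical ventilation"; baseline *Ureaplasma* is also named for the modelling. Birth size is not mentioned.
- **Statistical analysis, on the SAP:** "A statistical analysis plan will be developed prior to the end of the study".
- **Trial intervention:** infants, "within 72 h of birth, were treated intravenously for ten days with 20 mg/kg azithromycin for 3 days", then received a lower per-kg dose for 7 days; the placebo was made up and given in the same way.
- **Data from general practitioners (NNRD paragraph):** "Data collected includes information on initial neonatal admission as well as neurodevelopmental data at 2 years of corrected age". The variables are not itemised.
- **Discussion:** "We are collecting anthropometric measurements, including weight, length and head circumference at discharge"; the sentence goes on to cover measurements over the first 2 years from clinics and health visitors. Measurements at birth are not listed.

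**The concern.** Infants of the same sex and gestation can differ in size at birth, and birth size is likely to predict size at 1 and 2 years. Where a pre-treatment predictor of this kind is available, putting it in the model narrows the confidence interval for the treatment contrast. It also corrects for any chance difference in birth size between the arms.

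Two features of this study make the omission worth raising. First, growth is one of the main objectives, and the closing summary of the Discussion says that, if azithromycin improves survival without chronic lung disease, the study should have enough power to show an improvement in growth. No calculation supports that for growth: Tables 1 and 2 cover only wheeze and neurodevelopment. Second, the infants analysed will be those who survived to 36 weeks, had consent and have outcome data: about 500 of 799 randomised, or 500/799 = 63%. Balance in birth size is less assured in that subset than in the full randomised set.

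**Working it through.** **1. The planning number.** The Sample size section expects 70–75% outcome data from 700–725 survivors: 0.70 × 700 = 490 to 0.75 × 725 = 544, which it rounds to about 500. I take 250 per arm. The article's own figure for that size is a detectable difference of 12.7 percentage points at 80% power and alpha 0.05. With the continuity-corrected two-proportion formula, the required number is 251 per arm for wheeze (65% v 52.3%) and 254 for neurodevelopment (50% v 62.7%), against the stated 250. Without the correction it is 235 and 239. The figure therefore reproduces with the correction, but it concerns the two main outcomes and only supplies the expected number here. No sample size is stated for growth.

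**2. Growth without birth size.** Work in units of the residual SD after sex and gestation, since no SD is given. With two-sided alpha 0.05 and power 0.80:

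- detectable difference = (1.960 + 0.842) × √(2/250) = 2.802 × 0.0894 = 0.251 SD
- 95% confidence interval half-width = 1.96 × 0.0894 = 0.175 SD

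**3. Growth with birth size added.** Let r be the correlation of birth size with later size, given sex and gestation. The documents do not give it, so it is an assumption. The residual variance is multiplied by (1 − r²), the detectable difference by √(1 − r²), and the equivalent number per arm is 250/(1 − r²).

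| r (assumed) | Variance reduction | Detectable difference (SD) | Equivalent n per arm | Power at 0.251 SD |
|---|---|---|---|---|
| 0 | 0% | 0.251 | 250 | 0.80 |
| 0.1 | 1% | 0.249 | 253 | 0.80 |
| 0.2 | 4% | 0.246 | 260 | 0.82 |
| 0.3 | 9% | 0.239 | 275 | 0.84 |
| 0.4 | 16% | 0.230 | 298 | 0.86 |
| 0.5 | 25% | 0.217 | 333 | 0.90 |
| 0.6 | 36% | 0.201 | 391 | 0.94 |

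I use 0.2 to 0.5 as the working range; the outer rows show how the answer moves.

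**4. Chance imbalance.** With 250 per arm, the 95% limit for a chance difference in mean birth-size z-score is 1.96 × √(2/250) = 0.175 SD. Carried through to the outcome, that is 0.175 × 0.2 = 0.035 SD to 0.175 × 0.5 = 0.088 SD, or 14% to 35% of the 0.251 SD detectable difference. This is the same gain as in step 3 seen from another side, because the wider interval without birth size already allows for such imbalance. The two should not be added together.

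**5. Is the covariate available?** Per-kg dosing means that some early weight was known for each treated infant, in either arm. The NNRD holds data on the initial admission, subject to the optional database consent described under Screening and consent. Birth weight is therefore a sound inference. Birth length and birth head circumference are not listed as collected anywhere in the article.

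**The case against.** The strongest reply is that nothing here is wrong. A randomised comparison adjusted for sex and gestation is valid. The line on growth does not exclude other covariates, and the Statistical analysis section leaves room for further relevant factors. The SAP was still to be written. Since gestation and sex are already in the set, only the size-for-gestation part of birth weight adds information, and at r = 0.2 the gain is 4% of variance. Growth is not one of the two headline outcomes.

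Most of that stands, and it limits the point to efficiency. Two parts do not fully answer it. The room for further factors opens only after the univariable results are reported and does not name birth size; a covariate chosen then does not replace one named in advance. And the Discussion does claim adequate power for growth, so precision on that outcome matters to the study's own case.

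A reader might infer three stronger things that the article does not support:

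- *That precision is thrown away.* The adjustment set is not closed and the gain may be small.
- *That the baseline values of all three growth outcomes are already in hand.* Only an early weight can be inferred.
- *That discharge is the only measurement before 1 year, or is meant as the baseline.* The Discussion sentence continues to measurements over the first 2 years, the Design section names Red Book and clinic growth data, and nowhere is discharge size proposed as a covariate.

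**Conclusion.** The point holds as a modest loss of efficiency, with no bias from omitting birth size under intact randomisation. The stated growth adjustment omits birth weight, which can reasonably be expected to be available. With 250 per arm and an assumed r of 0.2 to 0.5, including it lowers the detectable difference from 0.251 SD to 0.246–0.217 SD, a variance reduction of 4 to 25%.

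The direction is secure; the size rests on the assumed correlation and on a number per arm taken from the other outcomes. Adjustment would also correct for imbalance in birth size among the infants with outcome data. A reader might infer that it would repair selective follow-up; it would not in general do so, since one covariate addresses only the part of any selection that runs through birth size.

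A related inconsistency needs settling in the same place: two-by-two tables and chi-square tests do not fit continuous measures that are to be adjusted for sex and gestation.

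**What to change.** In the SAP, replace the two-by-two tables and chi-square tests for growth with a prespecified model, for example:

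*Weight, height and head circumference at 1 and 2 years of corrected age will each be compared between arms by linear regression on treatment, sex, gestation and birth-weight z-score. For head circumference, birth head circumference will be added if it is recorded. Missing birth measurements will be replaced by the overall mean, calculated without regard to arm, so that no infant with outcome data is dropped.*

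For height, birth-weight z-score stands in for a birth length that the article does not show to be collected. Before finalising, confirm that birth weight is in the trial data or the NNRD extract, and for what share of infants.

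The cost is one model term (two for head circumference, if recorded) and a sentence on missing values. No new visits are needed; weight should come from records already made.
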